##### Caregivers

2.2.4.2

Adult family member (age 18 years and above) of a burn survivor or of those who passed away as a result of a burn injuryAble to provide consent and participate in the study

##### Health and emergency care professionals

2.2.4.3

Possess experience in managing burn casesCurrently working in a burn care centre and/or emergency care

##### Key informants

2.2.4.4

This will include community leaders and policymakers with exposure to and an understanding of burn prevention and burn care in Pakistan

#### Measures

2.2.5

Qualtrics software will be used for the online questionnaires. These questionnaires will be available in English, Urdu and/or other local languages of the participants (56, 57). A self-developed demographic questionnaire will be used to obtain information on the participants’ gender, age, level of education, marital status, native language, place of residence (rural and/or urban), employment status, self-reported general health and other variables. A unique tracking code will be developed to monitor each participant between measurements.

##### Knowledge Attitudes And Practice (KAP) Scale

2.2.5.1

The KAP includes a range of structured interviewer-administered questions to obtain a better understanding of knowledge, attitudes and practices regarding burn injuries (22, 34). The knowledge- and attitude-based questions include 10 items, scored on a four-point Likert scale ranging from strongly disagree to strongly agree. Higher scores represent better knowledge of and favourable attitudes toward burn injuries and first aid. The practice of burn first aid includes 12 questions with various response formats, such response categories such as ‘true/false’ and ‘yes/no’. A sample item for the knowledge-based questionnaire is, “Burns lead to permanent injuries?’ A sample item for the attitude-based questionnaire is, ‘Do you think that applying dough, oil, mud, toothpaste, etc. on the wound delays the healing process?’ A sample item for the practice of burn first aid is, ‘In case of a burn injury, have you ever applied cold water?’ The internal consistency, measured using Cronbach’s alpha, was 0.887 for the knowledge-based questionnaire, 0.716 for the attitude-based questions and 0.758 for the practical questions (22).

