**Methods and analysis:**

This cohort study will follow 600 participants (*n* = 600; *n* = 500 burn survivors; *n* = 100 caregivers) with three measurement points at 6- to 12-month intervals. The primary outcomes are knowledge, attitudes and practices regarding burn injuries. The secondary outcomes are meaning in life; gratitude, resentment and appreciation; hope; optimism; temporal satisfaction with life; coping strategies; social interaction anxiety; self-stigma and resilience, measured using the Meaning in Life Questionnaire, the Gratitude, Resentment and Appreciation Scale, the Adult Workers Hope Scale, the Patient Optimism Scale, the Temporal Satisfaction with Life Scale, the COPE Inventory, the Social Interaction Anxiety Scale, the Self-Stigma Scale and the Brief Resiliency Scale, respectively. The participants are grouped as follows: the exposure group (i.e., burn survivors [*n* = 200] and caregivers [*n* = 100] exposed to campaign messages), the non-exposure group (i.e., burn survivors [*n* = 250] not exposed to campaign messages) and the Photovoice group (i.e., burn survivors [*n* = 50] who participate in Photovoice and are exposed to the campaign messages). This design evaluates the impact of the health communication campaign and determines whether Photovoice has any additional effects on the primary and secondary outcomes.

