#### Procedure

2.2.3

The research team will recruit burn survivors and caregivers from 12 burn centres based in seven project sites across Pakistan to measure existing indicators of knowledge, attitudes and practices on burn prevention, as well as psychological variables, health information-seeking variables and demographics.

Burn survivors and their family members will be invited to fill out online questionnaires (baseline assessment). The research assistants will distribute posters and leaflets at participating centres and waiting rooms, introducing the study and providing the research team’s contact information for further enquiries. The research assistants will also attend the patient and/or family consultations to introduce the study and obtain consent for a follow-up call with the research team. During the follow-up call (within the first 24 or 48 h after the initial contact), the research assistants will ensure that interested burn survivors and their family members understand what their participation entails, and will confirm their willingness to provide informed consent. After informed consent is obtained, burn survivors and their family members will be asked to complete the same questionnaires at 6- to 12-month intervals up to a total of two times throughout the study (see Figure 2 for the CONSORT diagram). If they are literate, as determined during the informed consent process, they will receive a text message with a Qualtrics questionnaire link. If they are illiterate, a research assistant from the research team will call them for the completion of the questionnaires on the phone. Consent for collecting personal information will be obtained during the informed consent process.

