##### Photo reflection workshops

2.3.2.2

Participants will then be invited to the photo reflection workshops. They will be asked to bring three to five of their photos for individual reflection, which will be guided by the following photo-trigger questions: Describe what you see in this Photo: How does this photo make you feel? Why did you take a photo Of this? What does this photo Tell us about your experience with burns? How can this photo provide Opportunities for us and others to improve our lives. The participants will work individually with the facilitators to produce photo captions. At the end of the workshop, the participants will be asked to fill out a questionnaire package based on the baseline measures again and will be invited to the closed local exhibitions.

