##### Closed local exhibitions

2.3.2.3

Private exhibitions of the photos will be conducted at the participating centres. These exhibitions will be closed to the public for the following reasons: (1) to protect the participants’ identity, (2) to help build their confidence in displaying their photos, (3) to provide an opportunity to revise their photo captions and (4) to sign consent forms to have photos of themselves blurred/unblurred in preparation for public dissemination and exhibitions. The participants will be given 2 weeks to decide, if needed, and the research assistants will follow up with them. The participants will be asked to fill out the same questionnaire package based on the baseline measures at the end of the closed exhibitions.

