## End of project exhibitions (nationwide)

3

Finally, we will organise a series of end-of-project exhibitions across the designated research sites in Pakistan to which a broad range of stakeholders, community workers, carers, health care professionals, policymakers and journalists will be invited. With their consent, these end-of-project exhibitions will provide a platform for the participants and others exposed to Photovoice content to talk about their experiences. We will also liaise with journalists, TV presenters, radio programmers and bloggers to disseminate the exhibitions on a national scale. Participants who took part in the Photovoice process will be asked to fill out the same questionnaire package based on the baseline measures at the end of the public exhibitions.

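### The Photovoice group's t1 and t2 questionnaires are tied to the end of Photovoice events while the general procedure is a link or call at routine intervals, so the preliminary Photovoice effect absorbs any event-day shift; the stated KAP mode also conflicts with the procedure

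*Protocol article*

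**What the plan says.** The abstract states: "The primary outcomes are knowledge, attitudes and practices regarding burn injuries". Section 2.2.5.1 describes the KAP scale that measures them as "structured interviewer-administered questions".

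Section 2.2.3 sets the procedure for burn survivors and family members. After an online baseline, they repeat the questionnaires at intervals of 6 to 12 months. For literate participants, "they will receive a text message with a Qualtrics questionnaire link". For illiterate participants, "a research assistant from the research team will call them for the completion of the questionnaires on the phone".

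For the Photovoice group, follow-up is attached to events:

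- Section 2.3.2.2, photo reflection workshop: "At the end of the workshop, the participants will be asked to fill out a questionnaire package based on the baseline measures again".
- Section 2.3.2.3, closed exhibition at the participating centres: participants are asked to "fill out the same questionnaire package based on the baseline measures at the end of the closed exhibitions".
- Section 3, public exhibitions: "Participants who took part in the Photovoice process will be asked to fill out the same questionnaire package".

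The Table 1 footnote defines t1 as the end of the workshop and t2 as the end of the closed exhibitions. Section 4 takes its time points from Table 1. It computes Cohen's d for Photovoice as a difference between baseline-corrected estimated means over the pooled standard deviation.

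**The concern.** There are two problems of unequal weight.

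The smaller one is a contradiction about a primary outcome. For literate participants, the mode under which the KAP is described is not the mode in which it is collected.

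The larger one concerns comparability between groups. The abstract says that the design should show whether Photovoice adds anything to the campaign, which requires comparing the Photovoice group with groups that did not take part. If t1 and t2 are event-day answers in one group and routine-interval answers in the others, the contrast mixes the effect of Photovoice with the effect of being asked just after a Photovoice event. Self-reported attitudes, stigma, gratitude and social anxiety are plausibly sensitive to the occasion. The case is weaker for knowledge and first-aid practice items. Section 2.3.1.1 says that this component should prepare a larger evaluation and a future RCT, so a distorted d could be carried forward.

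**Working it through.** The protocol gives no figure on this point to reproduce. The first check sets the sections side by side.

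| | Photovoice group | Exposure and non-exposure groups |
|---|---|---|
| Baseline | Link or phone (2.2.3) | Link or phone (2.2.3) |
| t1 | End of workshop (Table 1, 2.3.2.2) | Link or phone, 6- to 12-month interval (2.2.3) |
| t2 | End of closed exhibition (Table 1, 2.3.2.3) | Link or phone, 6- to 12-month interval (2.2.3) |
| Further | End of public exhibition (3) | None described |

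What is certain and what is inferred:

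1. **Occasion: stated.** The Photovoice questionnaires follow an event in that group's own intervention.
2. **Interval: open.** The interval from baseline to each event is not fixed, so it may or may not fall within the 6- to 12-month window.
3. **Setting and mode: inferred.** The text does not say whether the event-day questionnaire is on paper, assisted, or the same link.

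Effect on the estimate. Let m be the event-day shift in SD units, present only in the Photovoice group and only after baseline:

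- expected baseline-corrected difference = true effect + m

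Correcting for baseline removes differences that were present at baseline. It leaves m, because m was not there. The demographic covariates in Section 4 do not describe the occasion of measurement and do not remove it either.

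Illustration of size. The document gives no value for m, so 0.1 to 0.3 SD is an assumption. The other inputs are the group sizes of 50 Photovoice and 200 exposed survivors (Section 2.1), the two-sided 5% level (Section 4), and the 20% dropout in the sample size paragraph, which gives 0.8 × 50 = 40 and 0.8 × 200 = 160.

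- SE = √(1/n₁ + 1/n₂): √(1/50 + 1/200) = 0.158; √(1/40 + 1/160) = 0.177.
- Smallest difference detectable with 80% power = (1.96 + 0.842) × SE: 0.443 SD and 0.495 SD.
- Probability of a significant result when the true effect is zero = 1 − Φ(1.96 − m/SE) + Φ(−1.96 − m/SE):

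| m (assumed) | 50 v 200 | 40 v 160 |
|---|---|---|
| 0.1 | 9.7% | 8.7% |
| 0.2 | 24.4% | 20.5% |
| 0.3 | 47.5% | 39.6% |

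This is an unadjusted two-sample approximation. To the extent that adjustment for baseline in the mixed model reduces the standard error, the same m would give higher rejection rates.

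**The case against.** The case on the other side has real content.

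- **Mode change is not documented.** Sending the usual link as the workshop closes would fit every section. A reader might infer supervised completion on site in front of facilitators, but the text does not say so. Facilitators are described as working with participants at the workshop, not as administering questionnaires, and the closed-exhibition section does not mention them. This stands: only the occasion is certain.
- **Literacy-based mode.** A reader might infer that splitting link and phone by literacy biases the group comparisons. Literacy-based mode is largely constant within a person, and the exposure and non-exposure groups use the same two routes. It is also a necessary accommodation. The exposure v non-exposure comparison is not affected by the event-day problem.
- **Event-day measurement has a purpose.** The Introduction names immediate as well as medium- and long-term effects. A lift just after the event may be part of the immediate effect. This stands as a reason to keep those questionnaires, but not to compare them with routine-interval answers.
- **The component is a pilot.** The protocol calls the Photovoice effects preliminary and gives no sample size calculation for them. This limits the weight of the point, although d is still planned and tested.
- **Photovoice participants might also receive the routine questionnaires.** Section 2.2.3 does not except them. Table 1, however, names the event-day questionnaires as t1 and t2, and Section 4 refers to Table 1.
- **The KAP wording may only describe the source instrument.** If so, one sentence resolves it.

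**Conclusion.** The point holds with a limited scope. The description of the KAP as interviewer-administered conflicts with the self-completed link for literate participants; this is a minor correction. The substantive fault is that t1 and t2 mean the end of a Photovoice event in one group and a routine interval in the others, so the preliminary Photovoice d would absorb any event-day shift in full.

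The size of that shift cannot be estimated from the document. The rejection rates of roughly 10% to 48% (50 v 200) rest on an assumed 0.1 to 0.3 SD and a true effect of zero; they show sensitivity and do not predict the bias. The conclusion assumes that Table 1 is followed as written and that d is a between-group contrast, as the aim of finding an additional effect of Photovoice implies. It should be changed before data collection, because an occasion that coincides with group cannot be separated from it in the analysis.

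**What to change.** 1. Base the Photovoice v exposure and Photovoice v non-exposure contrasts on questionnaires collected in all groups by the Section 2.2.3 route: the link, or a call from a research assistant who is not the participant's facilitator. Use the same 6- to 12-month window for all.
2. Redefine t1 and t2 in Table 1 to match, and give the event-day questionnaires their own labels.
3. Keep the end-of-event questionnaires as supplementary within-group data on immediate effects.
4. Record mode and setting at every wave for description. Do not rely on a time-varying mode term: if on-site completion occurs only at Photovoice follow-up, the term cannot be separated from Photovoice group by time.
5. Correct Section 2.2.5.1 to state the modes actually used for the KAP, and state how the end-of-event questionnaires are completed.

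The cost is some extra questionnaire burden for about 50 participants, one added data item per wave, and possibly a slightly lower response than at the event itself.

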##### Self-Stigma Scale (SSS)

2.2.5.2

The SSS (35) has both long (39 items) and short (9 items) versions, comprising three self-stigma subscales (cognitive, affective and behavioural), and is used to assess internalised stigma. In this scale, respondents rate their levels of agreement with each item (e.g., ‘My identity as a ______is a burden to me’ [cognitive], ‘I fear that others would know that I am a_____’ [affective], and ‘I estrange myself from others because I am a____’ [behavioural]) on a four-point Likert-type scale (1 = strongly agree to 4 = strongly disagree). The blank spaces on the scale were filled with ‘mental health consumer’ when used in a sample of mental health consumers and with ‘recent migrant’ when used in a sample of migrants (35). In this study, the blank spaces will be filled with the term ‘burn survivor’ to measure internalised stigma associated with this identity. Higher scores indicate greater self-stigma. Internal consistency estimates ranged from 0.87 to 0.91 for the total scale and from 0.80 (behavioural) to 0.84 (affective) for the subscales (29). Mean scores between 2.40 (SD = 0.66) and 2.41 (SD = 0.60) reflect moderate to high internalised stigma (35). More recently, the reliability of a shorter version of the scale (5 items) has been established, with Cronbach’s alphas of 0.93 and 0.91; it has demonstrated adequate convergent and criterion-related validity in an English-speaking sample in the US (36).

##### Meaning in Life Questionnaire (MLQ)

2.2.5.3

The Meaning in Life Questionnaire (MLQ) (37) assesses self-reported experiences of the presence of meaning and the search for it. The questionnaire consists of 10 items rated on a seven-point Likert-type scale ranging from 1 (absolutely untrue) to 7 (absolutely true). Some examples of items are ‘I have a good sense of what makes my life meaningful’ (presence of meaning) and “I am always searching for something that makes my life feel significant’ (search for meaning). The instrument has been shown to be reliable in various contexts, with Cronbach’s alphas ranging from 0.83 to 0.91 for both subscales (37, 38).

##### Gratitude, Resentment And Appreciation (GRAT) Scale

2.2.5.4

The GRAT Scale (39) will be used to measure the participants’ overall level of gratitude. This instrument measures participants’ lack of sense of deprivation (LOSD), simple appreciation (SA), and appreciation of others (AO) on a nine-point Likert-type scale ranging from 1 (strongly disagree) to 9 (strongly agree). LOSD is measured by items such as ‘Life has been good to me’, SA by items such as ‘Oftentimes, I have been overwhelmed at the beauty of nature’ and AO by items such as ‘I feel deeply appreciative for the things others have done for me in my life’. Across samples, this instrument has been shown to be reliable, with Cronbach’s alphas ranging from 0.88 to 0.94 on various subscales (39).

##### Adult Workers Hope (WHS) Scale

2.2.5.5

This scale focuses on work-related goals, pathways and agency (40). The WHS consists of 24 statements to which respondents indicate their degree of agreement. The item response format is a seven-point Likert-type scale ranging from 1 (strongly disagree) to 7 (strongly agree) and with the total scores ranging from 24 to 168 (40). Cronbach’s alpha coefficient was found to be 0.90 (40).

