Burn injuries affect not only the individual but also their family and community. Burn survivors experience long-term physical, psychological and social consequences (8, 10, 11). Longitudinal and experimental studies indicate that preexisting mental health conditions in both burn survivors and caregivers are closely related to survivors’ rehabilitation and psychological outcomes (12, 13). Many burn patients experience functional limitations shortly after the burn incident, limiting their ability to return to work or daily activities (11, 14). Burn incidents also affect patients’ families. Both patients and family members are at risk of developing post-traumatic stress disorder (PTSD) and experiencing guilt, stigma and discrimination, thus adversely affecting their quality of life (8, 11, 14). In countries where physical appearance is highly valued, burn survivors are often subject to harassment and negative, judgmental words (15). They experience increased distress in response to burn scars and other physical changes, leading to lower negative body image, self-esteem and social isolation (15).

There have been significant advancements in clinical burn care, the successful implementation of preventative initiatives and increased public awareness in high-income countries (16, 17). These advancements have led to a significant decrease in burn injuries and an increase in appropriate, high-quality care (16). Nonetheless, many LMICs still lack effective preventive measures, leading to persistently high rates of burn injuries (18–20). These injuries often occur without access to even the most fundamental health care, which can lead to avoidable fatalities, disabilities and social stigmatisation (18–20). In Pakistan, despite a population of more than 225 million and a high estimated incidence of burn injuries, insurance coverage and rehabilitative services are limited; this includes inadequate initial management of burn wounds and insufficient mental health care, leading to high rates of post-burn complications, such as contractures, PTSD and Common Mental Disorders such as anxiety and depression (21). Additionally, there is a lack of awareness of burn incidents and the challenges that burn survivors and their caregivers endure (21, 22).

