### Phase 0: baseline assessment

2.2

The research team will recruit participants (*n* = 600) from seven project sites across Pakistan for a baseline assessment measuring existing indicators of knowledge, attitudes and practices on burn prevention, psychological variables, health information-seeking variables and demographics (see Table 1 for the full list of variables).

**Table 1 tab1:** Outcome measures collected at the data collection points throughout the study.

Outcome measures	Baseline (t0)	Time 1 (t1)	Time 2 (t2)
KAP ^1,2^	X	X	X
SSS-S^1^	X	X	X
GRAT^1^	X	X	X
MLQ^1^	X	X	X
WHS^1^	X	X	X
CPOS^1^	X	X	X
TSWLS^1^	X	X	X
COPE^1^	X	X	X
SLAS^1^	X	X	X
BRS^1^	X	X	X
Photo Reflection^1,2,3,4*^		X	X
Campaign effectiveness^1,2,3,4^			X

Survivors^1^; family members ^2^; health care professionals^3^; key informants^4^; the photo reflection workshops are for burn survivors only except for the workshops conducted at the end of the public exhibitions^*^; t0, baseline; t1, end of photo reflection workshop; t2, end of closed exhibitions; t3, end of closed exhibition; t4, end of the final public project exhibition; KAP, Knowledge Attitude and Practice Scale; MLQ, Meaning in Life Questionnaire; GRAT, Gratitude and Resentment Scale; WHS, Adult Workers Hope Scale; CPOS, Patient Optimism Scale; TSWLS, Temporal Satisfaction with Life Scale; COPE, COPE Inventory; SIAS, Social Interaction Anxiety Scale; SSS, Self-Stigma Scale; BRS, Brief Resiliency Scale.

Ethical approval was obtained from the Pakistan National Bioethics (Approval ID: NBC-985) and Manchester University Research Ethics Committees (Approval ID: 2023–18,027-31199).

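### The secondary outcome hope is measured only with a work-specific scale given to all 500 survivors, so the score supports a claim about work-related hope, not hope in general

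*Protocol article*

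**What the plan says.** The Abstract (Methods and analysis) sets out the constructs: "The secondary outcomes are meaning in life; gratitude, resentment and appreciation; hope; optimism; temporal satisfaction with life". Hope carries no work qualifier there. The matching instruments follow in the same order, including "the Adult Workers Hope Scale, the Patient Optimism Scale, the Temporal Satisfaction with Life Scale", so the Adult Workers Hope Scale (WHS) is the one instrument for hope.

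Section 2.2.5.5 describes its content: "This scale focuses on work-related goals, pathways and agency (40"). It has 24 agreement items scored 1 to 7, "with the total scores ranging from 24 to 168 (40").

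Table 1 (section 2.2) marks the WHS with superscript 1 and an X at baseline, time 1 and time 2. The key reads "Survivors^1^; family members ^2^; health care professionals^3^; key informants^4", so the scale goes to survivors, with no restriction by employment. Section 2.2.4.1 admits adults with a recent or past burn and sets no employment condition.

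The Introduction says of many burn patients that functional limitations arise soon after the injury, "limiting their ability to return to work or daily activities". Section 2.2.5 collects "place of residence (rural and/or urban), employment status, self-reported general health and other variables". The demographic variables named for the mixed models in section 4 are age, education, gender, marital status, rural or urban location and household situation.

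**The concern.** The construct claimed is wider than the construct measured. A score built from statements about work can say something about hope concerning work. Whether it stands for hope in general, among people of whom some have no job or have lost one through the injury, needs support that the document does not give.

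There is also a route to misreading. Someone who returns to work between visits may well agree more with statements about work goals, whatever the campaign did. If employment differs between the groups, or changes at different rates in them, part of a difference in WHS score would be a difference in employment. The trial would then report it as an effect of the campaign or of Photovoice on hope.

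**Working it through.** **1. Stated figures.** The score range follows from items times response limits: 24 × 1 = 24 and 24 × 7 = 168, as stated. The number of survivors follows from the groups: 200 (exposure) + 250 (non-exposure) + 50 (Photovoice) = 500, as stated. No error lies in these figures. The article states no power or sample size for hope.

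**2. Outcome against instrument.**
- Outcome: hope, unqualified (Abstract).
- Instrument: work-specific (section 2.2.5.5), and the only one named for hope.
- Recipients: all survivors (Table 1), with no employment condition (section 2.2.4.1).
- Population: often limited in returning to work (Introduction).
- Adaptation: section 2.2.5.6 says the optimism scale was adapted for burn survivors, and section 2.2.5.2 says how the self-stigma items will be worded for them. Section 2.2.5.5 says nothing comparable about the WHS.

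**3. Can employment differ or change?**
- Between groups: sampling is snowball and purposive (section 2.2.1) and no randomisation is described. The Photovoice group must also be free to attend workshops (section 2.2.4.1), which may be related to employment.
- Over time: visits are 6 to 12 months apart (section 2.1), and some participants enter within 3 months of the burn (section 2.2.4.1). Return to work can therefore fall inside follow-up. Section 4 opens with a comparison of changes within groups. Such a comparison has no contrast that would cancel a shared trend in employment.

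**4. Possible size, on assumed inputs only.** The document gives neither employment rates nor a WHS gap between workers and non-workers. Assume the proportion employed differs between groups by 5 to 20 percentage points, and that the WHS gap is 0.3 to 0.8 SD. Then

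spurious difference = (difference in proportion employed) × (standardised WHS gap)

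- Lowest: 0.05 × 0.3 = 0.015 SD
- Middle: 0.10 × 0.5 = 0.05 SD
- Highest: 0.20 × 0.8 = 0.16 SD

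These are values before adjustment for the baseline score, which would reduce the part due to stable differences.

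**The case against.** A reader might infer that survivors without work cannot be validly scored. The document does not show this. Section 2.2.5.5 describes agreement statements about work and does not say that a current job is needed. A survivor off work can hold goals about returning. Validity in non-workers is unsupported here, not disproved.

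A reader might also infer that the hope result necessarily mixes employment with the campaign effect. That needs employment to differ between groups or to change differently in them. Return to work common to exposed and unexposed survivors cancels in a between-group contrast. Section 4 describes the baseline score as a usual covariate, and its list of demographic variables is open-ended. That list also serves moderation and mediation of behavioural intention, so it does not settle what enters the hope model.

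A third inference would be a specific loss of power. None can be derived, because the article gives no employment rate and no power for this outcome.

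The lack of a not-applicable code is no finding either, since such coding is commonly left to the analysis plan or the case report form. Missingness explained by a recorded variable can also be compatible with missing at random once the model conditions on that variable.

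Finally, the choice may be deliberate: the study objectives include prevention and risk assessment in workplaces and factories. That would be a good reason to measure work-related hope, but not to report it as hope in general.

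These objections limit the point to a mismatch and a risk. They do not remove the mismatch: the document names the outcome more broadly than its only instrument measures it, and gives no justification for doing so.

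**Conclusion.** The point stands in limited form. As planned, a conclusion about survivors' general hope would not follow from the WHS score. Employment is a plausible alternative explanation for a difference or change in that score. Its size is unknown; 0.015 to 0.16 SD illustrates it under the assumptions shown and is not an estimate for this study. The conclusion rests on the WHS being the only hope instrument, on its going to all survivors, and on employment not being named for its model. All three can be read from the article. The consequence is confined to one of nine secondary outcomes. The knowledge, attitudes and practices outcomes and the sample size calculation are untouched.

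**What to change.** 1. Name the outcome work-related hope wherever it is listed, and draw no conclusion on general hope from the WHS.
2. Keep all survivors in the main analysis. Include baseline employment status, already collected under section 2.2.5, as a covariate in the WHS model, and retain it whatever the stepwise AIC selection in section 4 would do.
3. Add a sensitivity analysis restricted to survivors employed or seeking work at baseline.

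Baseline employment addresses differences present at entry. It does not remove the effect of returning to work later. The narrower name matters most there, because a rise in work-related hope on resuming work is then not presented as a rise in hope at large.

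The cost is a narrower claim, one more covariate and a sensitivity analysis with fewer people. If 30% to 70% of survivors were neither employed nor seeking work (an assumption), it would hold 500 × 0.7 = 350 down to 500 × 0.3 = 150 survivors. In the Photovoice group it would hold 50 × 0.7 = 35 down to 50 × 0.3 = 15. For that reason the restriction belongs in a sensitivity analysis and not in the main one. No new data collection is needed.
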